### Baseline and outcome measurement at 0, 16, 26, and 52 weeks

Primary outcome:The primary outcome will be Cumberland Ankle Instability Tool (CAIT) assessed at 52 weeks. The CAIT is a 9-item 30-point scale, with a lower score indicating more functional ankle instability [42]. CAIT is a widely recommended discriminative instrument for the identification of CAI with good responsiveness [43]. A validated Chinese version will be used in this study [44].

Secondary outcomes:2)The total number of re-sprains in 1-year follow-up as assessed by a study-specific injury registry. Participants will be asked to send a digital message to the study coordinator in the event of an ankle sprain. An ankle sprain is defined as an ankle injury occurring as a result of sports participation or activities of daily living and which causes one or more of the following: participants have to stop the sports activity, and/or cannot (fully) participate in the next planned sports activity, and/or cannot go to work/school the next day, and/or needs medical attention (ranging from onsite care by, e.g., general practitioner, to personal care by, e.g., sports physician) [45].3)Self-reported function as assessed by the 29-item Foot and Ankle Ability Measure (FAAM): it includes two subscales: activity of daily living (21 items) and sports (8 items). The total score ranges from 0 to 100; a higher value means greater physical function [46]. Its validity has been demonstrated in CAI [47], and a validated Chinese version will be used in this study [48].4)Objectively measured balance, as assessed by the Star Excursion Balance Test (SEBT) [49]. To perform the SEBT, patients will stand on a single leg with the study limb placed at the center of a grid with 8 lines extending at 45° increments. They then attempt to reach the furthest possible point with one leg while maintaining balance on the contralateral leg. During the performance of SEBT, only the anterior (A), posterior-medial (PM), and posterior-lateral (PL) directions will be used. The distance from the center of the grid to the maximal reach point will be measured in centimeters with a measuring tape. Participants will be allowed 4 tries in each direction to get familiarized with the test and will be allowed to perform 3 reaches in each direction with 30-s rest between trials. The starting position will be randomly assigned to avoid a learning effect. The reaches in each direction will be normalized with the leg length. Lower limb length will be determined, with the subject lying supine, by measuring from the anterior superior iliac spine to the distal end of the medial malleolus. The SEBT composite score will be calculated by dividing the sum of the 3 reaches distances in the 3 directions by 3 times the limb length (LL) of the individual, then multiplied by 100 {[(A+PM+PL)/(LL×3)] }×100.5)Health-related quality of life as assessed by the 5-level of EuroQol 5-dimension questionnaire (EQ-5D-5L) [50]. Patients will be asked to self-rate their current health state on a visual analogue scale (EQ5D VAS) from 0 to 100. The EQ-5D-5L assesses five dimensions of current health: mobility, self-care, usual activities, pain/discomfort, and anxiety/depression (EQ5D index). A local study has evaluated the value set of the Hong Kong Chinese EQ-5D-5L questionnaire [51].6)To assess the success of blinding, participants will be asked to guess their group status at 52 weeks.7)Treatment satisfaction will be assessed at 52 weeks by a question “Are you satisfied with the treatment received?”.

Sociodemographic data such as age, sex, occupation, and imaging confirmed osteochondral lesions or post-traumatic osteoarthritis will be collected and controlled as con-founders.

### Sample size calculation

Since no previous studies have evaluated the role of DPT in CAI, we estimated our sample size based on the paper by Weight et al. which calculated the minimal clinical important difference (MCID) of CAIT in a group of athletes with CAI. In this paper, the mean change of CAIT after focused ankle rehabilitation interventions, i.e., wobble board balance training and resistance tubing strengthen training, was 4.4 (SD 5.1) whereas the control group without any intervention was −1.4 (SD 3.4), yielding Cohen *D* of 1.34 [52]. Since the sample size of Weight’s et al. was small (*n*=50), the assessment period was short (only 4 weeks), and their participants were very young (mean age 21.5), we assumed a more conservative effect size for DPT of 0.60. With alpha 0.5 and power 85%, the calculated sample size will be 102. With the dropout rate of 10%, the total sample size will be 114, with 57 at each arm.

### Statistical analysis

We will conduct an analysis of covariance (ANCOVA) to compare the CAIT score at 52 weeks between the intervention groups with adjustment of the baseline CAIT score. For the secondary analysis, we will use ANCOVA for other secondary continuous outcome measures and logistic regression for the binary outcome. To study the trend, we will conduct generalized estimating equations models (GEE) for both primary and secondary outcomes following the intention to treat principle, i.e., all available data will be analyzed according to the group they are randomly assigned. The use of GEE also provides the means to include subjects with incomplete and use all available data to assess the treatment effect over time. Given the longitudinal nature of the clinical trial data, we assume the autoregressive covariance structure will be the best fit for the data, but the statistical fitness by using other covariance structures will also be evaluated [53].

With a clearly defined target population, efficacy and safety outcomes, and convenient data collection procedures, our trial should realize the goal of maximizing the number of participants who are maintained on the protocol-specified intervention until the outcome data are collected. We will use multivariate imputation using chained equations (MICE) to incorporate auxiliary information about the missing data. The imputation model will include prerequisite variables in the data analysis. About 10 iterations will be conducted in each imputation process with more iterations to be considered until the chain reaches convergence [54]. Twenty completed datasets will be imputed with the use of the chain equations. Rubin’s rule will be applied to combine the effect estimates [55]. This approach provides estimated standard errors and *P* values that incorporate missing-data uncertainty. We will use the statistical package SPSS version 24 (SPSS Inc., IL, USS). All statistical tests will be two-tailed with a significant level of 0.05.

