**Methods and analysis:**

A single-center, parallel-group, randomized controlled trial will be conducted at a university-based primary care clinic in Hong Kong. A total of 114 patients with CAI will be randomly allocated (1:1) to DPT and NS groups. The primary outcome will be the Cumberland Ankle Instability Tool scores at 1 year. The secondary outcomes will be the number of re-sprains in 1 year, the Star Excursion Balance Test, the 5-level of EuroQol 5-dimension questionnaire, and the Foot and Ankle Ability Measure. All outcomes will be evaluated at baseline and at 16, 26, and 52 weeks using a linear mixed model.

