Dextrose prolotherapy (DPT) is an injection used to treat chronic painful musculoskeletal conditions through stimulation of tissue proliferations [14–17]. It consists of injections of hypertonic dextrose with a concentration between 10 and 25% to ligament-bone or tendon-bone system or in the intra-articular space, which is performed repeatedly at the established interval. Pre-clinical studies have suggested its mechanism of actions through initiation of a temporary inflammatory reaction with cytokine-induced tissue repair, granulation, soft tissue proliferation, and extracellular matrix remodeling [18–20]. The exposure of human tenocytes to DPT had been shown to induce an inflammatory response through the up-regulation of pro-inflammatory mediators [21]. In mouse models, DPT was found to stimulate fibroblast proliferation through activation of the Erk Pathway [22]. Soft tissues such as ligaments and collagen bundles also demonstrate a larger cross-sectional area and a better tensile strength after DPT [23–25].

Clinically, DPT has been used to treat conditions with specific soft tissue-mediated joint instability. Its strengthening effect on anterior cruciate ligament laxity had been proposed in a small clinical trial with patients having knee osteoarthritis [26, 27]. In a prospective single-arm study, patients with sacroiliac joint instability receiving DPT injections to the dorsal interosseous ligament have shown functional improvement for up to 24 months [28]. DPT provided significant relief of pain in patients with sacroiliac joint instability, and with longer effect than steroid injections [29]. Overall, rigorous evidence supporting DPT for ligament injuries is lacking; trials are limited in number, often of short duration, and lack methodological rigor.

This study aims to assess the clinical efficacy of DPT compared to normal saline injections among individuals with CAI in a randomized controlled trial (RCT). Our hypotheses are that DPT, compared with blinded saline injection, will result in improved self-reported ankle instability, function, and quality of life; reduced total number of re-sprains; and improved objectively assessed function over 1 year.

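### Re-sprains in one year are a count, but the named models are for continuous or binary outcomes, a GEE without family, link or offset, or a linear mixed model; the event definition does not name the study ankle

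*Protocol article*

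**What the plan says.** The outcome section of the Protocol article defines the second outcome as "The total number of re-sprains in 1-year follow-up as assessed by a study-specific injury registry". The abstract lists it first among the secondary outcomes, and the Introduction hypothesises a "reduced total number of re-sprains" on dextrose. Events reach the registry through self-report: "Participants will be asked to send a digital message to the study coordinator in the event of an ankle sprain". The event definition begins "An ankle sprain is defined as an ankle injury occurring as a result of sports participation or activities of daily living" and goes on to the consequences that qualify an injury as an event. It does not mention side.

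Three statements bear on the analysis:

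- Statistical analysis, on secondary outcomes: "we will use ANCOVA for other secondary continuous outcome measures and logistic regression for the binary outcome".
- Statistical analysis, on trend: "we will conduct generalized estimating equations models (GEE) for both primary and secondary outcomes following the intention to treat principle". An autoregressive structure is the expected choice, with alternatives to be examined. No distribution, link or offset is given.
- Abstract, Methods and analysis: "All outcomes will be evaluated at baseline and at 16, 26, and 52 weeks using a linear mixed model".

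Missing data are to be handled by chained-equation imputation with 20 datasets. The sample size section allows 10% dropout.

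**The concern.** Each participant contributes one cumulative total, built up from events after enrolment. It has no week-0 counterpart, so the abstract's model with a baseline and three later values cannot be fitted to it. The main text does not name a linear mixed model at all. If the total is treated as continuous, ANCOVA ignores time at risk. If it is treated as binary, repeat events are lost, although the hypothesis concerns the total number. GEE could be set up for a count, but a single yearly total has no within-person series for an autoregressive structure, and the elements that would make it a rate analysis are not fixed.

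Time at risk matters because a participant who stops sending messages looks the same as one with no further sprains.

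The definition raises a second issue. An injection into one ankle is not expected to prevent sprains of the other. If both sides enter the count, the treatment effect is diluted. The balance test in the same section does refer to the study limb; the sprain definition does not.

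At stake is a stated hypothesis whose test can still be chosen among several models once the data are in.

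**Working it through.** **Inputs.** From the protocol: 57 per arm, two-sided 0.05, 10% dropout. The planned totals of 102 and 114 concern the CAIT score, so there is no figure for re-sprains to reproduce. Assumed: yearly means of 1.0 (control) and 0.5 (dextrose), with negative binomial shape 1, so the variance is μ + μ². Power is Φ(|effect|/SE − 1.96).

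**1. Count model, full follow-up.** Var(log RR) = [(1/1.0 + 1) + (1/0.5 + 1)]/57 = 5/57 = 0.0877, SE 0.296. log 2 = 0.693; 0.693/0.296 = 2.34; power Φ(0.38) ≈ 65%. Simulation (1,500 trials) gave about 68%.

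**2. Any v none.** P(any) = 1 − 1/(1 + μ): 0.500 v 0.333. SE = √[(0.250 + 0.222)/57] = 0.091; 0.167/0.091 = 1.83; power Φ(−0.13) ≈ 45%. Simulation: 43-44%.

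**3. Linear model on the raw count.** Variances are 2.0 and 0.75. SE = √(2.75/57) = 0.220; 0.5/0.220 = 2.28; power Φ(0.32) ≈ 62%. Simulation: 65-66%, about 2 points below the count model.

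At means of 2 v 1, simulation gave 80-81% (count), 78-80% (linear) and 44-45% (any v none).

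**4. Follow-up.** Further simulations used control means of 0.5, 1 and 2 and dispersions of 0.5 and 1.5, with dropouts leaving at times spread evenly from 0.05 to 1 year (mean 0.525) and their partial counts kept. The negative binomial model took the dispersion as known.

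| Scenario | Linear, raw count | Negative binomial with offset |
|---|---|---|
| No effect, dropout 10% in both arms | 4.3-5.5% reject | 4.6-5.3% reject |
| No effect, dropout 5% v 25% | 5.9-8.6% reject | 4.4-4.7% reject |
| Rate ratio 0.5, dropout 10% in both arms | 38-88% power | 39-90% power |

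The reason is visible in the mean exposure: 1 − 0.05 × 0.475 = 0.976 years v 1 − 0.25 × 0.475 = 0.881 years. The raw counts then show a ratio of 0.881/0.976 = 0.90 with no treatment effect. With a milder imbalance, 15% v 5% leaving at mid-year, the ratio is 0.925/0.975 = 0.95.

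**5. Other-ankle events.** Assume that 30% of control events are in the other ankle and unaffected by treatment. The study-ankle means are then 0.70 v 0.35, and the all-ankle means are 1.00 v 0.35 + 0.30 = 0.65.

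- Study ankle only: Var = (1/0.70 + 1 + 1/0.35 + 1)/57 = 6.286/57 = 0.110, SE 0.332; 0.693/0.332 = 2.09; power ≈ 55%.
- All events: Var = (1/1.00 + 1 + 1/0.65 + 1)/57 = 4.538/57 = 0.0796, SE 0.282; log(1/0.65) = 0.431; 0.431/0.282 = 1.53; power ≈ 33% (simulation 33-34%).

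The like-for-like loss is therefore about 21 points. Comparing 34% with the 68% of step 1 would overstate it, because step 1 places every event in the study ankle.

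**The case against.** A reader might infer that the plan offers nothing beyond ANCOVA and logistic regression. It does: GEE is planned for the secondary outcomes as well, and with a log link and an offset it can analyse counts. What remains is that the protocol ties GEE to trend and does not fix those elements. Family and link alone might be left to an analysis plan. Here, though, the article does state methods, they do not match its first secondary outcome, and the abstract names a model that the main text does not.

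A reader might also infer that re-sprains will be dichotomised. The protocol does not say so. Its single binary outcome could be another item, such as the satisfaction question. The 44% is the cost of one route left open, not of a stated choice.

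Nor is the linear model plainly invalid. With balanced 10% dropout its type I error is near nominal and its power loss small. The distortion needs strongly unequal dropout, whereas the protocol gives only an overall 10%. Imputation could also remove it: in the same simulations, restricting the linear model to participants with full follow-up gave 4.0-4.8% rejection under 5% v 25% dropout. That requires partial counts to be declared missing, which the protocol does not state, and dropout there was unrelated to sprain risk.

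Finally, the definition does not say that other-ankle sprains are counted. The word re-sprain can be read as the ankle already injured. The wording is open, not wrong.

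**Conclusion.** The point holds as a mismatch between outcome and stated methods, plus a conflict between abstract and main text. It does not show that the planned result would be wrong. Under the assumed rates, most is lost if the count is reduced to any v none: about 68% to 44%. A linear model costs about 2 points with balanced follow-up and becomes unreliable, at about 6-9% type I error, only with strongly unequal dropout. Counting both ankles would move a rate ratio of 0.50 to 0.65 and power from about 55% to 34%, if 30% of control events were in the other ankle. The rates, the dispersion, the dropout imbalance and the 30% share are all assumptions; the protocol supplies none of them. The primary outcome and the sample size are unaffected. It should be fixed because a stated hypothesis otherwise has no fitting prespecified test.

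**What to change.** Before allocation is revealed:

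- Name one analysis for re-sprains: negative binomial regression with treatment as factor and log(time at risk) as offset, reporting the rate ratio with 95% CI. Take re-sprains out of the ANCOVA, GEE and mixed-model statements.
- Define when time at risk ends for participants who leave early, and state that partial counts enter with their exposure rather than being imputed as well.
- State that the outcome counts study-ankle events, and tabulate other-ankle events separately.
- Reconcile the abstract's linear mixed model with the Statistical analysis section.

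The cost is wording, since the model is a standard generalised linear model. The drawback is somewhat fewer counted events. A question on sprains and side at visits would now help little: recruitment ended in December 2021 and the last visit is expected on 5 March 2023, so only remaining visits could use it. If the registry did not record side, it would have to be established while everyone is still blinded.

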## Safety monitoring

Participants will have a diary to document any discomfort after each injection. Potential injection risks include bleeding, infection, and nerve injuries. Participants are advised to call or WhatsApp the study coordinator if they are uncertain whether the discomfort is related to the injections. Standardization forms will be used for monitoring and reporting side effects and adverse events. The principal investigator will be present in case of a significant adverse event. The principal investigator will report serious adverse events to the ethics committee within 24 h, and annual reports summarizing adverse events will be submitted to the Drug Office of the Department of Health, Hong Kong Administrative Region. A “stopping rule” will be applied to participants who underwent ankle surgery or experienced severe adverse events during the study period [56].

### Data monitoring committee

A data monitoring committee is formed for data quality assurance, monitoring, and reporting. The team is composed of a senior clinical researcher with rich experience in clinical trials, an Orthopedic surgeon, and a Family Medicine Specialist. A research assistant and a nurse will also be members of the QA team. Interim data monitoring will be done by a biostatistician who is not a co-investigator to monitor the quality of the study every 3 months.

### Monitoring and quality assurance

The coordinating center is composed of the principal investigator (physician), nurse, and research team member and are responsible for monitoring the whole trial process. They will meet every week to discuss the trial process and any problem that was encountered during the trial. The data will be stored in a password-protected cloud server and only the principal investigator and research team member have access to the dataset.

## Dissemination

The findings of this RCT will be disseminated through presentations at public lectures, scientific institutions, and meetings and through peer-reviewed scientific articles. The de-identified data with statistical codes can be obtained from the corresponding author upon reasonable request.

## Discussion

Apart from foot and ankle rehabilitation on muscle strengthening, balance, proprioception, and correction of biomechanics, conservative treatment options for CAI are limited, and surgery is an effective option when conservative treatment fails; drawbacks include the risk of surgical complications and relatively higher costs [57]. DPT, with reported pain and function effects for other musculoskeletal soft tissue injuries, and potential regenerative effects on soft tissue injury, may be an alternative treatment option to those who failed conservative management of CAI. Dextrose is inexpensive and readily accessible, and the injection of ATFL can be easily performed by trained physicians with or without ultrasound. The efficacy of DPT, as measured by validated self-reported instability, function and quality-of-life, and objectively assessed-functional outcomes in this trial, will further inform its role in clinical practice.

## Trial status

The first approved protocol was on 23 October 2019 and the latest approved protocol is version 4 on 11 March 2022, by the Joint Chinese University of Hong Kong – New Territories East Cluster Clinical Research Ethics Committee. Recruitment began in February 2021 and was completed in December 2021. The last patient visit will be expected on 5 March 2023. The protocol was initially submitted before the completion of recruitment; however, the review process was much delayed due to COVID-19 and other administrative issues. The protocol is now submitted to *Trials*, and the last patient visit for outcome assessment will be on 5 March 2023.

## Data Availability

The de-identified data with statistical codes and the relevant results in this study will be shared through academic conferences and scientific papers. The datasets can be obtained from the corresponding author upon reasonable request.

## Abbreviations

LAS: Lateral ankle sprain
CAI: Chronic ankle instability
DPT: Dextrose prolotherapy
NS: Normal saline
ATFL: Anterior talofibular ligament
RCT: Randomized controlled trial
CAIT: Cumberland Ankle Instability Tool
PI: Principal investigator
D15: 15% dextrose
FAAM: Foot and Ankle Ability Measure
SEBT: Star Excursion Balance Test
A: Anterior
PM: Posterior-medial
PL: Posterior-lateral
LL: Limb length
EQ-5D-5L: 5-Level of EuroQol 5-dimension questionnaire
VAS: Visual analogue scale
MCID: Minimal clinical important difference
ANCOVA: Analysis of covariance
GEE: Generalized estimating equations models
SD: Standard deviation
